#### Cost measures

We will collect cost data to determine total intervention cost under enhanced linkage and standard-of-care arms, as well as the costs of HIV-related health services or other costs incurred up to 12 months following the receipt of HBHCT, using methods previously developed by the research team [9, 79]. Costs will be assessed in three categories: (i) direct costs of HBHCT & linkage activities, (ii) HIV care costs incurred as a consequence of HBHCT & linkage activities, and (iii) time-costs and out-of-pocket expenses incurred by individuals receiving the intervention. For the direct costs of HBHCT and linkage activities, data on personnel time and consumables will be extracted from staff activity logs, and data on training costs, transportation, and management/administrative overheads will be collected from program records. For the costs of additional HIV care and laboratory services incurred as a consequence of the intervention, costing will be undertaken at HIV clinics to establish unit costs for clinic visits, ART and other medicines, and routine laboratory tests. The number and timing of HIV-related services received by study participants will be collected from clinic records. Wages and other input prices will be based on public sector values to ensure that results are applicable to routine program settings. During the 12-month follow-up interviews we will include questions to determine costs incurred by study participants in relation to receipt of the intervention and HIV care (including time costs, travel costs, and any out-of-pocket payments related to HIV care).

#### Monitoring intervention fidelity

Counselors will use electronic intervention protocols programmed on tablets to guide them in completing the components of each intervention session. For each step they will document its completion by selecting potential outcomes or typing in a description, e.g., “primary barrier is fear of being seen at clinic;” “no noted potential adverse events.” This will allow us to capture the percentage of intervention protocol steps that the counselor delivered. We have used this method to monitor intervention fidelity in previous intervention research in Uganda [80].

**Table 3 Tab3:** Data collection, measures, data sources

Data element	Timeframe	Data source/ instrument	Data collected	Collected from
Brief demographic assessment	Baseline	Self-report	Sociodemographics (gender, age, education, economic and marital status, religion, etc.); prior access to health services (e.g., HIV testing, circumcision among men); HIV stigma; fertility desires and contraception (pregnancy status, number of living children, number of additional children wanted, contraceptive use)	• All individuals consenting to HBHCT and baseline questionnaire interview
Follow-up assessments	6 months, 12 months	Self-report Clinic records^a^	Linkage and time to HIV care^a^; co-trimoxazole and ART initiation & time to initiation^a^; short-term retention in care^a^; tuberculosis^a^; ARV adherence^a^; HIV disclosure; receipt of instrumental and emotional social support; HIV stigma (anticipated, enacted, internalized; subjective health status; perceived need for treatment; barriers to accessing care; health care system literacy; beliefs about traditional and western medicine; patient-provider relationship and clinic wait time; acceptance of HIV diagnosis; alcohol use; depression; positive and negative life events following HIV testing; intimate partner violence	• Intervention trial participants (intervention and control group)
Brief follow-up assessment	12 months	Self-report	Clinic attendance; CD4 results, taking co-trimoxazole and ART	• Viral load and CD4 only group
Biological measures	Baseline, 12 months	Laboratory report	• HIV status (baseline) • Viral load (baseline, 12 months) • CD4 cell count (baseline,12 months)	• Intervention trial participants (intervention and control group) • VL and CD4 only group
Clinic-level data	Twice monthly	Checklist	Drug stock-out: Availability of all ARVs and cotrimoxazole	• All participating HIV clinics
Costing data – service utilization	Ongoing (collected in program records and clinical data)	Program records Clinic records Log-book	• Receipt of HBHCT home visits, counseling visits, follow-up contacts • HIV care services (clinic visits, lab tests, ARVs)	• Intervention trial participants (intervention and control group)
Costing data – service unit costs	Year three of trial	Program accounts, micro-costing at HIV clinics	Intervention related costs – personnel time, consumables, infrastructure, overheads	• Study administration, participant HIV clinics
Costing data – patient costs	12 months	Self-report	Costs incurred by participants related to intervention and/or HIV care	• Intervention trial participants (intervention and control group)
Intervention fidelity	Daily	Electronic protocol checklist	Percentage of intervention sessions steps completed	• Intervention counselors

Note: ^a^ indicates follow-up assessment items measured through both participant self-report and clinic records. ARV: antiretroviral; *HBHCT* Home-based HIV counseling and testing; VL: viral load

### Data analysis approach

Univariate statistics will be conducted on primary and secondary endpoints as well as covariates to describe the sample characteristics for the two study arms. Attrition in the two arms will be compared. Multiple imputation technique will be implemented and sensitivity analysis will be conducted.

To assess the primary outcome (the proportion of participants who are virally suppressed at 12-months) and secondary outcomes (linkage to care, time to care, receipt of opportunistic infection prophylaxis, and initiation of ART among those eligible for ART at baseline), linear mixed models and nonlinear mixed models will be applied. Information criterion such as Akaike information criterion or Bayesian information criterion will be used for model selection.

In evaluating the intervention effectiveness mechanisms, and mediators and moderators, we will use structural equation modeling to estimate the causal effects using growth mixture modeling to account for the longitudinal and clustered data. To assess an existence of moderators of an intervention effect, covariates such as disclosure, social support, HIV stigma, adherence, distance from the clinic, CD4 count, having other HIV-positive household members, number and duration of intervention sessions received, village-level stigma towards PLHIV, etc. will be included. A nonlinear mixed model will be fitted independently for each covariate plus the treatment variable and an interaction term between the covariate and the treatment.

To examine the natural history of stages in the HIV care continuum, we will use the control group to identify barriers to and facilitators of linkage to care and treatment, retention, and viral suppression, potential predictors include: sociodemographics, HIV stigma, disclosure, etc. Stepwise forward selection method from both logistic regression model and general linear model will be used to identify potential significant predictors for our analyses. Predictors that are selected from the stepwise method will be included in our mixed models.

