This paper describes the protocol for a cluster-randomized controlled trial (CRCT) to test an enhanced linkage to care intervention during HBHCT in rural Uganda. Our Providing Access To HIV care (Providing Access to HIV Care (PATH)/ *Ekkub*o) intervention enhances a similar strategy tested by Coates, Wanyenze, Bangsberg, and colleagues [39] that was found to reduce time to HIV care and treatment among patients receiving opt-out HIV testing in health facilities in Uganda. The intervention facilitated linkage by: providing orientation to the HIV care system, counseling to help clients identify and reduce barriers to engagement in care, and assistance disclosing and identifying a treatment supporter. The PATH/Ekkubo intervention described in this paper enhances the original intervention in order to increase its impact on multiple outcomes, including HIV viral suppression, and adapts the intervention to address barriers specific to HBHCT by providing additional counseling with increased emphasis on HIV stigma reduction through increased social support. We test this intervention in a CRCT, with randomization at the level of the village rather than at individual level, to avoid potential contamination since village residents interact with one another regularly in our study setting. The specific aims are:Compare the efficacy of the enhanced linkage to care intervention (PATH) vs. standard-of-care (paper-based referrals) at achieving individual and population-level HIV viral suppression, and intermediate outcomes of linkage/time to care, time to/receipt of ART. We hypothesize that the PATH intervention study arm will have a higher proportion of participants who are: a) virally suppressed at 12-month follow up, and will have shorter time to: b) HIV care and c) ART initiation, among those eligible, than the standard-of-care study arm. We also hypothesize that the effect of the intervention on HIV viral suppression will be mediated by intermediate behavioral outcomes: linkage to care and ART initiation. Finally, at the cluster level, we hypothesize that villages randomized to the intervention arm will have higher rates of population-level HIV viral suppression than those in the standard-of-care study arm at 12-month follow-up.Using the standard-of-care group as a natural history control, collect longitudinal data on barriers to and facilitators of linkage to and retention in care and treatment and HIV viral suppression.Estimate the cost and cost-effectiveness of the intervention, as compared to standard-of-care HBHCT, in terms of: viral suppression, linkage to care, and receipt of ART.

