### Study design

The trial design is a matched-pair two-arm, cluster-randomized design with clusters being villages. One arm is the PATH/Ekkubo intervention arm and the other is a standard-of-care (control) arm. Villages are randomized to study arms. We will include 40 villages with approximately 600 participants across all clusters (villages). We will conduct structured interviews at baseline (pre-intervention), and at six and 12-month follow-up. Similarly, blood draws for HIV viral load and CD4 testing will be done at baseline and at 12-month follow-up. The design is illustrated in the CONSORT Diagram, Fig. 1.

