#### Secondary outcome measures

Our main secondary outcome measures include HIV care linkage, ART initiation, and short-term retention in care (detailed below) collected through participant self-report at six and 12-month follow-up interviews, supplemented by clinic records and direct observation of participants’ HIV clinic cards and ART pill bottles where possible.
*Linkage and time to care* (six and 12 months, clinic records). We will assess linkage to care with data on: enrollment in an HIV clinic, having a second HIV clinic visit, and time from HIV testing to enrollment in care at an HIV clinic.
*ART initiation & time to initiation* (six and 12 months, clinic records). To assess receipt of HIV treatment we will determine if participants have been prescribed and have taken ART and the time from HIV testing to ART initiation. We will determine the percentage of participants eligible for ART (currently CD4 < 500 until the guidelines [8] to expand eligibility are implemented nationwide), who received antiretrovirals (ARVs) based on their CD4 count taken at the time of HBHCT, as well as the time from diagnosis to ART initiation. If possible, interviewers will directly observe the participant having ARVs at their home and review the patient’s HIV clinic record card to confirm self-reported data.
*Short-term retention in care* (six and 12 months, clinic records)*.* We will assess the following retention measures that have demonstrated the best discriminatory capacities for predicting viral suppression [45, 46]: a) missed visit count: number of missed visits accrued (count measure) based on scheduled visits determined by MOH clinical guidelines, b) visit adherence: proportion of kept visits/scheduled visits (kept + missed visits) (continuous measure, range = 0.0–1.0), and c) four-month visit constancy: number of four-month intervals with at least one kept visit (categorical measure, range = 0–3).

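### Growth mixture modelling is the wrong device for the longitudinal and village-clustered structure of the aim 1 mediation analysis; a cluster-aware path model on the same data would test the hypothesis

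*Protocol article*

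**What the plan says.** In the protocol article, Data analysis approach, the paragraph on mechanisms names structural equation modelling as the estimator of causal effects, "using growth mixture modeling to account for the longitudinal and clustered data". The hypothesis this must serve is in the Background under the first specific aim, that the "effect of the intervention on HIV viral suppression will be mediated by intermediate behavioral outcomes: linkage to care and ART initiation".

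The measurement schedule for that pathway is as follows.

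- Outcome: the Study design section says that "blood draws for HIV viral load and CD4 testing will be done at baseline and at 12-month follow-up". Data analysis approach defines the primary outcome as "the proportion of participants who are virally suppressed at 12-months", a binary variable at one time point.
- Mediators: the Secondary outcome measures section takes linkage from the 6- and 12-month interviews and clinic records, including the time from testing to enrolment in care. For treatment it will record "if participants have been prescribed and have taken ART and the time from HIV testing to ART initiation".
- Other mechanism variables (Independent variables section): social support is measured at 6 and 12 months. Stigma is measured at baseline, 6 and 12 months, but participants who do not report being HIV positive at baseline receive a partly different set of items there.

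The article does not say to which series the growth mixture model is fitted, how many classes it has, or how village enters it. The primary and secondary outcomes are assigned to mixed models, and the moderator interactions to nonlinear mixed models.

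**The concern.** The sentence gives growth mixture modelling a specific job, and the method does not do that job. Its latent classes are unobserved groups of individuals with similar trajectories. They are not villages, and a single-level growth mixture model has no between-village variance term. If clustering is handled at all, a multilevel component or a robust variance does it, and the article names neither for this analysis.

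The method also needs repeated measures of something that changes along a trajectory. On the aim 1 pathway the outcome has two occasions at most, and the mediators are onsets. Trial entrants are newly diagnosed or have never linked to care, so linkage does not vary at baseline.

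At stake is the mechanism result that the Discussion promises if the intervention works. An analyst who followed the sentence literally would have to rescue the model with constraints and a number of classes chosen after seeing the data. The indirect effects would then depend on those choices.

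**Working it through.** The article gives no figure for this analysis to reproduce. The check is a count of identified quantities, followed by a check that a simpler model can be estimated.

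1. **Linear growth on viral load, one class.** With T occasions there are T means and T(T+1)/2 variances and covariances.
   - T = 2 (baseline and 12 months, Study design): 2 + 3 = 5 moments. A random intercept and slope need 2 growth means, 3 growth variances and covariance, and 1 residual variance, so 2 + 3 + 1 = 6 parameters, or 7 with a residual variance per occasion. The rank of the moment equations is 5, so the model is not identified.
   - T = 3: 3 + 6 = 9 moments against 6 or 8 parameters, with full rank. The third occasion makes the difference.
   - Adding classes does not help. Within a class, the 3 observed variances and covariance must still supply 4 variance parameters (3 growth, 1 residual).

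2. **Latent classes on binary suppression.** K classes over T occasions need (K − 1) + KT parameters, and the data give 2^T − 1 free cell probabilities. For K = 2 and T = 2 that is 1 + 4 = 5 against 4 − 1 = 3, so two classes are not identified.

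3. **A restricted exception.** A two-class normal mixture on continuous log10 viral load, with class-specific means, one common covariance matrix and no separate residual variance, has 1 + 4 + 3 = 8 parameters. At illustrative values its information matrix has rank 8, so it is identified, but only through the assumed normal shape within classes.

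4. **Mediators.** Linkage and ART initiation each happen once and carry a date. That suits a time-to-event variable or an indicator by a fixed time, not a growth curve.

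5. **Can the hypothesis be tested without a growth model?** Arm → linkage → suppression needs one mediator value and one outcome value per person. An illustrative simulation used 40 villages of 12, 500 runs and assumed effects with village variation in both mediator and outcome. The indirect effect was a product of coefficients with village-clustered standard errors. The mean indirect effect was 0.095, its empirical standard deviation 0.0235 and the mean clustered standard error 0.0238. The effect sizes are assumptions; the run shows only that the model can be estimated and its standard error is sound. It does not include pair matching or unmeasured confounding.

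6. **Scale of village clustering, for context.** The sample size section gives k = 0.24, suppression of 55% and 75%, an average cluster of 14 and 18% attrition. ICC = k²p/(1 − p) gives 0.0576 × 0.55/0.45 = 0.070 and 0.0576 × 0.75/0.25 = 0.173. With 14 × 0.82 = 11.48 analysed per village, 1 + 10.48 × ICC = 1.74 to 2.81. This is a design effect for the total effect of arm on suppression and applies only if villages were ignored. It is not the variance inflation of an indirect effect, and it takes no account of matching.

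**The case against.** The strongest reply is that structural equation modelling is the planned estimator and that the sentence states an intent to account for clustering. A condensed article may leave the way village enters to the analysis plan, and multilevel growth mixture models and cluster-robust structural equation models both exist. This stands. A reader might infer that the mediation hypothesis cannot be tested as planned, or that the standard errors will ignore villages. The document supports neither inference.

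Nor does any section say that the growth mixture model is fitted to viral load. The Discussion names a further pathway through social support and stigma, and stigma has three nominal occasions with one short anticipated-stigma scale listed at each. The count of 5 against 6 does not apply there, although it is debatable whether the baseline items are comparable. A reader might also take the mediators to have only 6- and 12-month values. They are in fact dated, with clinic records as a source. Finally, item 3 of the working shows that a claim of non-identification for every possible mixture would be too strong.

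What the reply does not remove is the mismatch in the stated method. Further detail in an analysis plan can add a multilevel or robust component, but that component would then do the work the sentence assigns to growth mixture modelling. For the pathway aim 1 names, neither the outcome nor either mediator offers three comparable, varying occasions.

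**Conclusion.** The point holds in a limited form. Growth mixture modelling does not by itself account for village clustering, and in its usual form it is not identified for the aim 1 pathway on the schedule given. The counts rest on two viral load occasions and on a linear growth model with random intercept and slope; they need no assumed effect sizes. The mediation hypothesis itself remains testable with the structural equation approach already named.

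The consequence is confined to the mediation analysis. The comparison of arms on the primary and secondary outcomes and the tests of moderator interactions are not affected. No numerical bias in the indirect effect can be derived from the document, and the factor of 1.74 to 2.81 should not be read as one. The change is worth making because the sentence misstates the method for a hypothesis under aim 1 and the correction is cheap.

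**What to change.** For the aim 1 pathway, drop the growth mixture step and specify a multilevel or village-cluster-robust mediation (path) model:

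- exposure: study arm;
- mediators: linkage to care and ART initiation, dated from clinic records and required to precede the 12-month viral load;
- outcome: viral suppression at 12 months;
- covariates: baseline variables already collected, such as viral load, CD4 count, sociodemographics and distance to clinic;
- inference: standard errors that reflect the matched-pair village design, for example a bootstrap that resamples village pairs. Forty villages give 20 pairs, so the small number of units should be considered when intervals are chosen;
- sensitivity analysis: unmeasured confounding between mediator and outcome, because randomisation does not protect that link.

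If growth mixture modelling is kept for another mechanism variable such as stigma, the plan should name the series, justify that its occasions are comparable, fix how the number of classes is chosen, and state how village enters.

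The cost is a change of wording in the analysis plan and modest extra analysis work. No new data, visits or participants are needed.

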#### Independent variables

*Sociodemographics* (baseline). We will assess participants’ gender, age, tribe, educational level, socioeconomic status, employment status, income, religion, gender, marital/partnership status, distance to clinic, and travel time to the clinic.
*Prior use of health services* (baseline). We will measure prior use of HIV services, including history of HIV testing, frequency, location, and reasons for health service use in the prior 6 months, male circumcision for men, and location of births for women.
*CD4 cell count* (baseline, 12 months)*.* CD4 cell count will be assessed via venous blood draws along with VL at baseline and 12-month follow-up. Baseline CD4 values may affect viral suppression success [47]. We did not include CD4 as an outcome measure because according to recommendations by WHO and the United States Department of Health and Human Services, when VL is available, CD4 has little added value for monitoring treatment adherence and efficacy of ART [44, 48].
*Tuberculosis (TB)* (six and 12 months, clinic records). We will assess co-infection with TB using questions adapted from the MOH’s HIV clinic card. Interviewers will use the participant’s clinic card and self-report to record if the participant is TB infected, date of diagnosis, and treatment initiation and regimen.
*ART adherence* (six and 12 months). We will assess self-reported adherence to ART using the Adult AIDS Clinical Trials Group scale [49], which includes recall questions about ARVs missed for the previous 4 days prior to the interview, as well as 17 items assessing participants’ main barriers to adherence. It has demonstrated construct validity in Uganda and similar settings [50].
*Disclosure of HIV-test results* (six and 12 months). We will measure HIV status disclosure with an instrument used in prior research in Uganda and other African countries [39, 51]. It asks about the disclosure of serostatus to spouses, sexual partners, family members, community members/leaders, physicians, etc. The proportion of participants reporting each disclosure is calculated after eliminating those who say the disclosure was not applicable to them.

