*Depression* (six and 12 months)*.* We will measure depression symptoms using a modified 20-item version of the Center for Epidemiological Studies scale [74], which has been shown to be reliable in a rural Ugandan sample (α = 0.90) [75].
*Positive and negative life events following HBHCT* (six and 12 months). We will include items to assess life events following HIV testing using items by Grinstead et al. [76] and used in our prior work in Uganda [39]. The scale assesses the occurrence of life events since diagnosis, such as the strengthening of a relationship, breakup of a relationship, physical abuse by a sexual partner, and neglect by family.
*History of intimate partner violence* (six and 12 months). Items assessing experience of intimate partner violence originating from the Conflict Tactics Scale [77] and included in the WHO multicountry study [78] will be included. The scale includes 10 questions asking participants if they experienced any emotional (e.g., has he/she ever insulted you or made you feel bad about yourself?), physical (e.g., has he/she ever kicked you, dragged you, or beaten you up), and sexual violence (e.g., has he/she physically forced you to have sexual intercourse when you did not want to?) from a partner ever, and in the prior 12 months.
*Intervention contamination* (six and 12 months)*.* We will ask participants what type of counseling they received and from whom (to assess potential contamination) and the number of HIV-positive household members and if they are in care and on treatment. We will keep records on the number of and duration of intervention sessions each intervention arm participant actually received.
*Clinic level factors* (twice monthly)*.* We will monitor ART and cotrimoxazole stock outs at the participating clinics and hospital, where participants will most frequently visit to pick up their medications, on a twice-monthly basis through use of a checklist that includes of all drugs routinely prescribed for HIV-positive individuals.

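### Variables that arise after the intervention starts are tested as moderators; within-level arm effects are open to bias, and the sessions-by-arm interaction cannot be estimated

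*Protocol article*

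**What the plan says.** The third paragraph of Data analysis approach names the moderators: "To assess an existence of moderators of an intervention effect, covariates such as disclosure, social support, HIV stigma, adherence", then distance from the clinic and CD4 count, and finally "having other HIV-positive household members, number and duration of intervention sessions received, village-level stigma towards PLHIV, etc. will be included". It also fixes the model: "A nonlinear mixed model will be fitted independently for each covariate plus the treatment variable and an interaction term between the covariate and the treatment".

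Other sections of the protocol article show when these variables come into being:

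- **Independent variables** schedules disclosure, social support and ART adherence at six and 12 months only. Table 3 agrees.
- **PATH/Ekkubo intervention arm** and Table 2 make disclosure planning, support seeking and coping with stigma part of the counselling itself.
- **Independent variables**, under intervention contamination, says of sessions: "We will keep records on the number of and duration of intervention sessions each intervention arm participant actually received". HIV testing procedures restricts control counsellors to standard-of-care linkage in control villages.
- **Discussion** proposes to test social support as protective against stigma, with onward effects on linkage, treatment and suppression. That is a mechanism.

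**The concern.** A moderator should be a characteristic that the intervention cannot have changed. Then the arms remain comparable within each of its levels, and a difference in arm effect between levels describes who benefits.

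Disclosure, support and adherence at follow-up are not of that kind. Those who disclosed in the intervention arm and those who disclosed unaided in the control arm may differ in ways that also affect suppression. Comparing the arms within disclosers, or within non-disclosers, conditions on a consequence of treatment. Adherence adds a selection step: it is defined only for people who started ART, which is itself a secondary outcome.

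Sessions received raises a simpler problem, because the variable does not vary in the control arm.

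At stake are the moderator and mechanism results, which the Discussion says will be useful for developing future interventions. They could be reported as guidance on whom to target when they do not support that reading.

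**Working it through.** The plan gives no figure to reproduce here. Three checks apply.

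**1. Status of each listed variable**

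| Variable | When available | Usable as a moderator? |
|---|---|---|
| Distance from the clinic | Baseline | Yes |
| CD4 count | Baseline and 12 months | Yes, baseline value |
| Village-level stigma | Baseline village mean | Yes |
| Other HIV-positive household members | Asked at six and 12 months | Only if ascertained at baseline |
| Individual stigma | Baseline (items depend on known status), six and 12 months | Not the follow-up values |
| Disclosure, social support | Six and 12 months | No; intervention targets |
| Adherence | Six and 12 months, only after ART start | No |
| Sessions received | Intervention arm, after allocation | No |

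**2. The sessions model**

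Let A = 1 for intervention and 0 for control, and let S be the number of sessions. The stated model has columns 1, A, S and A×S.

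- Intervention arm: A×S = 1×S = S.
- Control arm with S = 0: A×S = 0 = S.

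So S = A×S for every participant. A numerical check with 300 per arm gave rank 3 of 4. If software drops the duplicate column, the remaining S coefficient is the slope within the intervention arm and not an interaction. If controls are coded missing instead, they leave the model; A is then constant and the arm effect is lost too.

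The within-arm slope is itself confounded. The optional sessions at weeks 8 and 10 go to those still unlinked at week six, and the clinic booster takes place only if the client attends. Session count thus depends on linkage, a secondary outcome, and the two rules push in opposite directions.

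**3. How large the distortion could be**

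All parameters here are assumptions, not protocol figures, and clustering is left out.

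*Simulation A (n = 2,000,000).* U is an unmeasured N(0,1) trait and T is arm. Disclosure D = 1 if U + e + 0.7T > 0.3, so disclosure rises from 42% to 61%. Suppression follows logit P(Y) = 0.2 + U + bT.

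| b | Stratum | Control | Intervention | Difference | Odds ratio |
|---|---|---|---|---|---|
| 0 | D = 0 | 0.443 | 0.392 | about -5 points | 0.81 |
| 0 | D = 1 | 0.680 | 0.636 | -4.4 points | 0.82 |
| 0.9 | D = 0 | 0.443 | 0.588 | +14.5 points | 1.79 |
| 0.9 | D = 1 | 0.679 | 0.795 | +11.6 points | 1.83 |
| 0.9 | Overall | 0.541 | 0.714 | +17.3 points | 2.12 |

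Example of an odds ratio: (0.392/0.608)/(0.443/0.557) = 0.645/0.795 = 0.81. With no true effect, both strata show apparent harm. With a true effect, both strata understate it.

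*Simulation B (n = 600, 400 runs, risk-difference scale).* The model is Y on arm, M and arm×M. M is a binary variable shifted by the intervention, M has no effect on Y, and there is no true effect modification.

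| Scenario | True arm effect | Arm coefficient at M = 0 | Interaction | Rejected at 5% |
|---|---|---|---|---|
| No shared cause | 0.12 | 0.116 | 0.003 | 5% |
| Shared cause, acting alike in both arms | 0.12 | 0.080 | 0.003 | 4.5% |
| Shared cause, weakened by the intervention | 0.12 | 0.186 | -0.149 | 35.5% |
| As above, no arm effect | 0 | 0.067 | -0.152 | 36% |

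**The case against.** The strongest reply is that these are exploratory analyses, that the bias is conditional, and that the list contains sound moderators. Much of this stands.

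- **Bias needs a shared cause.** Without one, Simulation B shows no bias. The results are open to bias; a reader might infer that they are bound to be artefacts, but that does not follow. Distance, baseline CD4 and baseline village stigma are valid.
- **A false interaction is not automatic.** From the differences of +14.5 and +11.6 points a reader might infer that Simulation A demonstrates spurious moderation. It does not on the logit scale, the natural one for a binary outcome in a nonlinear mixed model: the odds ratios are nearly equal (0.81 and 0.82; 1.79 and 1.83). What it shows is a distorted arm effect within strata. A false interaction appeared only under the further assumption that the intervention changes how the shared cause drives the variable.
- **Mediation is not left without a method.** The paragraph says "we will use structural equation modeling to estimate the causal effects using growth mixture modeling", and viral load has only two occasions, so a reader might infer that the mediation hypothesis has no workable estimator. The document does not support that. Structural equation modelling is named, and the mediators in the aims, linkage and ART initiation, are dated and supplemented by clinic records. A path model needs no growth curve.
- **The non-estimable term shows itself when fitted.** True, but the plan then gives no rule for what replaces it.

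An article may leave detail to an analysis plan. Here, however, it states both the variables and the model, and the measurement schedule provides no baseline version of disclosure, support or adherence.

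**Conclusion.** The point holds in a limited form. Disclosure, social support, adherence and sessions received are wrongly placed as moderators. For the first three, arm effects within levels are open to bias wherever the variable and suppression share causes, and they cannot be read as showing who benefits. The size depends on assumptions: in the scenarios run, the arm coefficient at M = 0 ranged from undistorted, through 0.080, to 0.186 against a true 0.12. For sessions received the conclusion is exact algebra given controls coded zero: rank 3 of 4 and no estimable interaction. The article also gives social support and stigma two roles, moderator in the analysis section and mechanism in the Discussion.

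Nothing here touches the primary or secondary comparisons of arms, and nothing supports extending the criticism to the whole moderator list.

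**What to change.** Change the moderator paragraph as follows.

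1. Limit interaction models to variables fixed before the intervention: baseline CD4, distance from the clinic, baseline village-level stigma, and household HIV status only if ascertained at baseline.
2. Move disclosure, social support, follow-up stigma and adherence to the mediation analysis already planned, and state its assumption of no unmeasured confounding between mediator and outcome.
3. Remove number and duration of sessions from the interaction models. Report them descriptively, or use a complier-average (instrumental variable) analysis with allocation as the instrument and a compliance definition set in advance. If a within-arm dose-response is shown, say that it is confounded, because session count depends on linkage and clinic attendance.

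The cost is wording and fewer moderator tests. On the schedule described, no extra data are needed; household HIV status stays out of the interaction models if it has no baseline record.
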